**Table 1 Tab1:** **Intervention domains and sample text messages**

Domain	Sample text message
Improving a sense of social support	Stay strong. The clinic cares about you.
Ameliorating negative affect	Everyone feels sad sometimes. Remember you can talk to your provider about depression.
Bolstering positive affect and coping	Smile, breathe, and go slowly.
Fostering empowerment	Be active in your health care. Keep your scheduled appointments.
Supporting healthy behaviors and health maintenance	Invest in your health. Remember to get your Pap smear.
Emphasizing the value of antiretroviral adherence and persistence	Taking meds? They help, even if you can’t tell they are working.

Additional formative work included a pilot phase to test technical and administrative aspects of field operations, as well as the acceptability of intervention text messages. We obtained feedback on one month of messages from participants enrolled in an open-phase pilot (n = 10) to further refine intervention content. These pilot participants then entered an extension phase in which main study procedures and instruments were tested with this group, so as to resolve any technical glitches prior to deployment with main study participants. Pilot participant data will not be analyzed with that of randomized study participants.

Intervention messages are divided into three response types. Type 1 is a message that asks for no response (one-way). Type 2 asks participants if they found the message helpful (two-way). Type 3 asks participants if they would like more information on a topic and if they answer yes, they receive a message with additional information (three-way). Each domain has messages from each response type, and domain-specific messages are randomly ordered over the twelve-month intervention period. Intervention group participants receive at least one Type 2 or 3 message per week because we track responses to estimate the amount of intervention participants receive. Participants can choose morning, afternoon, or evening times to receive intervention messages.

### Efficacy outcomes

#### Primary outcome

The primary outcome is virologic suppression at 12 months, defined as a viral load <200 copies/μL [28].

### Key secondary outcomes

A three-level ordinal retention variable that incorporates an assessment of *missed visits* as well as *six-month visit constancy*.○ High: Attended all scheduled primary care appointments in both 6-month study periods○ Moderate: Attended at least one scheduled clinic appointment in both 6-month study periods○ Low: Attended no scheduled clinic appointments in at least one 6-month study period*Visit adherence rate*, defined as the number of primary care appointments kept divided by the number of appointments scheduled, excluding cancelled or rescheduled visits.

### Other secondary outcomes

Depression symptom severity [31]Positive affect [32]Perceived social support [33]Health-related quality of life [34]Health care empowerment [25],[35]

The rationale for assessing several measures of retention is that retention measures generally fall into two categories, those based on missed or “no-show” visits and those based on kept visits. It is deemed standard by experts in the field to use at least one measure from each category when conducting research on retention in care as these measures are thought to capture different aspects of the retention in care experience [36].

### Process outcomes

Response rate to monthly check-in “blast”Response rate to Type 2 and 3 intervention messagesPercentage of time in study without cell phone service

As is true of many randomized trials, C4C exists on the continuum between efficacy and effectiveness [37]. Efficacy studies determine whether an intervention produces the expected result under ideal circumstances and effectiveness studies measure the degree of beneficial effect in “real world” settings [38]. C4C only enrolls patients who are in clinical care and willing to participate in a research study, potentially resulting in a less generalizable sample that is more consistent with an efficacy study. However, it does not provide participants with cell phones or airtime, which acknowledges that service interruptions (and thus interruptions in the intervention) represent “real world” implementation. This study decision was based on an emerging area of importance in behavioral (non-pharmacologic) interventions [39] and text messaging studies in particular [40] – that of process evaluation, which seeks to determine whether the intervention was delivered as intended and whether participants engage with the intervention.

Participants may experience disruption in receiving SMS appointment reminders and intervention messages due to cell phones being lost or stolen, participants’ inability to pay their bills, or participant loss to follow-up. We therefore plan to track the frequency of responses to monthly check-ins for all participants and for Type 2 and 3 messages in the intervention arm. We will also record self-reported loss of phone access at study check-ins by phone and at in-person study visits.

### Challenges in intervention implementation

All C4C text messages are sent using the text messaging platform of an outside vendor. The initial text messaging vendor did not have the capacity to conduct the study as planned and thus two months into the main study the C4C team transitioned to using the open-access platform Twilio to send text messages manually until the platform of the new vendor could be deployed, which occurred six months into the main study. While enrolled participants experienced no break in study messages, we will examine the effect of vendor on efficacy during analysis.

### Data collection and management

The primary efficacy outcome of virologic suppression at 12 months will be defined by the clinic EMR closest to the study visit. Patients who do not have EMR results available within 4 weeks of the final 12-month study visit will receive phlebotomy at the study visit.

EMR data will also be used to assess the secondary efficacy outcome of retention in care. One of the shortcomings of this technique is that it measures retention in a particular clinic rather than true retention in care, which could potentially occur in multiple clinics. The EMR used in this study identifies primary care visits to other clinics in the San Francisco Department of Public Health system, which will help address this issue. If during study follow up participants indicate that they have transferred care outside of this system, we will seek their permission to obtain appointment records from the outside clinic. Scheduled and kept primary care appointments after transfer elsewhere be included in the assessment of retention; consequently, we anticipate that missing outcomes will be rare (Table 2).

**Table 2 Tab2:** **Use of clinic and study data sources to ascertain study outcomes**

	Retained in C4C study	Lost to C4C study
Retained in care	Viral load and appointment data available from EMR, outside clinic records, and, when necessary, study phlebotomy	Viral load and appointment data available from EMR and (if permission obtained) outside clinic records
Not retained in care	Phlebotomy performed to collect viral load data	Tracking attempted at study end to ascertain missing outcomes

Laboratory and appointment data downloaded from clinical and hospital EMRs will be de-identified. Viral load results from study phlebotomy are transmitted to study staff in a secure spreadsheet. Baseline and follow-up questionnaires include validated psychosocial measures, including measures required by the funder’s cross-site data harmonization effort [41]. Study questionnaires also include questions about cell phone access and use. Study questionnaires are self-administered through Computer Assisted Survey Information Collection (CASIC), a web-based data collection tool, and have both computer-assisted personal interviewing (CAPI) and audio computer-assisted self-interviewing (ACASI) components. Outbound text messages and incoming responses from participants are captured in daily logs, as are failed attempts at SMS transmission to participants. A data manager merges all study data based on participant ID and performs periodic quality control for range and completeness of data. All participant data is stored on a secure password-protected server.

### Study procedures

#### Recruitment

A daily EMR query allows a research assistant to identify patients who may qualify for the study and remind providers that a particular patient may be eligible. Clinic providers introduce the study to patients and refer interested individuals to a research assistant. While explaining the study in more detail, the research assistant asks the patient to read a sample text message, enabling a brief literacy check. The research assistant assesses an individual’s visit history in the EMR and uses a checklist to complete screening with the patient. If individuals do not have viral load results or results pending in the EMR within the past four weeks, they can undergo phlebotomy through the study. Once eligibility is confirmed, individuals are scheduled to visit a community-based research site located in the Tenderloin neighborhood, where many patients reside, in order to complete informed consent, a baseline questionnaire, phone activation in the vendor platform, and randomization. To facilitate this visit, the research assistants offer same-day baseline study appointments and a bus token. Participants are reimbursed $30 cash for their time after completing baseline, 6 and 12 month study visits. They are not given phones nor are they compensated for any costs associated with the messages. If individuals are interested in the study but do not own a cell phone, research assistants refer them to the federal Assurance Wireless program, which assists low-income individuals in obtaining cell phones (http://www.assurancewireless.com/Public/Welcome.aspx).

#### Randomization

At the baseline study visit, a research assistant reviews and confirms eligibility in a study database. Following written consent, a computer program captures the enrollment time and uses unpredictable specific digits to allocate patients 1:1 to study arms. Equal allocation occurs within levels of the stratification factor (HIV diagnosis within the past 12 months vs. greater than 12 months). We stratified by this factor because the estimated virologic suppression rate for individuals newly diagnosed with HIV infection in San Francisco is higher than national averages and may exceed the rate among individuals with longer standing HIV diagnoses [42]. In addition, to maximize allocation concealment and ensure balanced allocation throughout accrual, equal allocation also occurs within randomly generated blocks of size 4, 6 or 8.

#### Blinding

As outlined by Boutron et.al., study staff cannot be blinded to intervention allocation because monitoring study participation may require follow-up phone conversations, and participants cannot be blinded because of the differential frequency and type of SMS messages by arm [39].

#### Follow-up of study participants

Follow-up study visits occur at a community-based research site rather than in the same building as the clinic in order for the study to avoid influencing attendance at clinic visits. Both intervention and control arm participants are asked to complete 6 and 12 month study visits, at which time participants complete a self-administered questionnaire that collects secondary outcomes. If no viral load is resulted or pending in the EMR from the past 28 days then phlebotomy is performed for viral load assessment. Participants receive check-in phone calls at 3 and 9 months to remind them of the upcoming study visit and confirm that the participant’s contact information remains up to date (Figure 2).

**Figure 2 Fig2:**
[figure not shown]
**Timeline for data collection by study month.**

Follow-up study visits are scheduled to occur in two-month windows around the 6 and 12 month mark [15]. However, we acknowledge the many challenges inherent in working with a marginalized urban population in a year-long study. If we are unable to contact participants but they present to the clinical research site for follow-up, we will perform data collection as outlined in Figure 2.

### Statistical methods

#### Sample size

Based on clinic data [43], we designed the trial assuming a rate of virologic suppression of 60% at 12 months in the control arm. To detect an improvement of 15% in the intervention arm with 80% power and a two-sided α = 0.05, we calculated that we would need 152 participants per arm (or, 167 participants per arm assuming 90% 12-month study retention, based on the experience of other studies using the same population). Clinic data from 2013 demonstrated that at least 552 unique patients would be eligible for the study by viral load and primary care visit criteria. This calculation underestimates the actual pool of eligible patients because it excludes those who lack a viral load measurement within 28 days prior to a primary care visit. Based on trial experience during the first nine months of recruitment, we expect that approximately 10% of patients will be ineligible due to cell phone criteria and another 10% will decline participation. Given a planned accrual period of 21 months, we anticipate that the pool of eligible patients is sufficient to satisfy the target of sample size of 304.

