## Methods

### Study design

C4C is a single site, parallel arm, open-label RCT of SMS appointment reminders alone vs. SMS appointment reminders plus thrice-weekly SMS messages that deliver information and enhance motivation and psychosocial adjustment. Eligible consenting patients are allocated 1:1 to the two arms within strata defined by HIV diagnosis within the past 12 months (i.e. “newly diagnosed”) vs. earlier (Figure 1).

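### The recruitment target of 304 carries no allowance for loss, so the stated 80% power holds only if every participant has a 12-month viral load

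*Protocol article*

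**What the plan says.** All the figures stand in the Sample size section of the protocol article.

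- Control rate: "we designed the trial assuming a rate of virologic suppression of 60% at 12 months in the control arm".
- Effect and error rates: "To detect an improvement of 15% in the intervention arm", "with 80% power and a two-sided α = 0.05".
- Number before loss: "we calculated that we would need 152 participants per arm".
- Number after allowing for loss: "167 participants per arm assuming 90% 12-month study retention". The section attributes the 90% to experience in other studies of the same population.
- Target: "we anticipate that the pool of eligible patients is sufficient to satisfy the target of sample size of 304".

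The Study design section adds equal allocation: "Eligible consenting patients are allocated 1:1 to the two arms within strata".

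Three other places bear on how many participants will have the primary outcome. Data collection and management takes the viral load from the clinic electronic medical record (EMR), with study phlebotomy where no recent result exists, and expects few missing outcomes. Table 2 adds outside clinic records, if permission is given, and tracking at study end for those lost to both clinic and study. The Analysis plan says that suppression status is missing only in that last group.

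**The concern.** Within one paragraph the plan gives two totals, 304 and 334, and adopts the smaller without saying why. The smaller is the number that must be analysed, yet it is used as the number to be enrolled. The same passage sets it against the pool of eligible patients, the expected phone-related ineligibility and refusals, and a 21-month accrual period, all of which are recruitment quantities.

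The power of the primary comparison is at stake. If some of the 304 have no 12-month viral load, the comparison rests on fewer than 152 per arm and falls below the stated power. As written, a reader cannot tell how many participants the trial means to enrol, or what power it has under the loss that it allows for.

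**Working it through.** **Inputs.** p1 = 0.60, p2 = 0.75, two-sided α = 0.05 (z = 1.960), power 80% (z = 0.8416), 1:1 allocation, 90% retention, target 304. The 15% is read as percentage points. That reading reproduces the plan's 152, whereas a relative 15% (69% against 60%) would need 443 per arm.

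**Step 1: reproduce the plan's figure.** Two proportions, pooled variance under the null, no continuity correction, mean rate 0.675:

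n = [1.960 x √(2 x 0.675 x 0.325) + 0.8416 x √(0.60 x 0.40 + 0.75 x 0.25)]² / 0.15²

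= [1.960 x 0.6624 + 0.8416 x 0.6538]² / 0.0225 = 151.87, so 152 per arm.

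This matches exactly. Power at 152 is 80.03%, so rounding up leaves no spare participants.

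**Step 2: identify the target.** 2 x 152 = 304. The section's own loss-adjusted total is 2 x 167 = 334.

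**Step 3: power when 304 are enrolled.** Power = Φ[(0.15 x √m − 1.960 x 0.6624) / 0.6538], where m is the number per arm with a 12-month viral load:

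| Outcomes missing | m per arm | Power |
|---|---|---|
| 0% | 152 | 80.0% |
| 2% | 148.96 | 79.2% |
| 5% | 144.4 | 78.0% |
| 10% | 136.8 | 75.7% |

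Only the 10% row uses a loss figure from the plan, and it equates loss to the study with loss of the outcome. The 2% and 5% rows are assumptions that show the range, since the plan puts no number on missing viral loads.

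**Step 4: detectable difference.** With 136.8 per arm, a 60% control rate and 80% power, the formula in Step 1 gives about 15.7 points in place of 15.

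**Step 5: sensitivity to the formula.** At 136.8 per arm, power is 76.5% (unpooled variance), 76.0% (arcsine) and 74.2% (log relative risk). No choice restores 80% at 10% missing. The unpooled formula needs 150 per arm, so under it 304 would tolerate only about 1% missing (2 of 152).

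**Step 6: the inflated number.** To keep 152 evaluable at 90% retention, 152 / 0.90 = 168.9, so 169 per arm (338). The plan's 167 leaves 167 x 0.90 = 150.3 per arm and 79.6% power, 0.4 points short.

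**Step 7: eligible pool.** 552 eligible patients less 10% for phone criteria and 10% for refusals is 552 x 0.80 = 441.6, about 442. This exceeds 304, 334 and 338.

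**The case against.** The strongest reply is that study retention and outcome ascertainment are different things. The 90% is retention in the study. A participant who stops attending study visits but stays in care still has a viral load in the EMR or, with permission, in outside records, and someone lost to both is sought at study end. On that design 304 may be deliberate, with 167 per arm quoted only as an alternative.

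Much of this stands. A reader might infer that the trial has 76% power and not 80%; the documents do not support that flat statement. The 76% applies only if the whole 10% lost to the study also lack a viral load from every other source. Nor do the documents show that the allowance was dropped by mistake.

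The reply does not remove the inconsistency. The Sample size section does not appeal to EMR capture; it applies 90% retention to the primary-outcome calculation and then leaves it out of the target. Since 152 has no margin, the reply works fully only with no missing outcomes, and the plan itself expects few, not none. Eligibility favours people who are new to the clinic or poorly retained there, outside records need permission, and tracking is an attempt without a guaranteed result.

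Two further inferences are tempting. One is that 167 is a serious miscalculation from 152 x 1.10 = 167.2. That source is unconfirmed, because 150 / 0.90 also gives 167, and the effect is 0.4 points of power. The other is that a larger target could not be recruited; the pool of about 442 covers every candidate total.

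**Conclusion.** The point holds in a bounded form. The stated power and the stated target do not agree under the loss allowance given in the same paragraph. With 304 enrolled, power for 75% against 60% lies between about 76% (10% of outcomes missing) and 80% (none missing), and is about 78% at 5%. At the lower end the chance of missing a true 15-point effect is about 24% instead of 20%.

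This rests on the plan's own rates, on reading the improvement as absolute, and on the pooled two-proportion formula that reproduces 152. Where in the range the trial falls depends on how complete the 12-month viral loads are, which the article does not quantify. The analysis method and the type I error are not affected. The figure of 167 per arm is a minor correction.

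**What to change.** Name one target in the Sample size section and give the power that belongs to it.

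- **If 304 is kept:** state that power is about 76% at 90% ascertainment of the 12-month viral load and reaches 80% only with complete ascertainment. Add the completeness expected from the sources in Data collection and management, Table 2 and the Analysis plan, and on what evidence.
- **If 80% power at 90% ascertainment is wanted:** state the loss-adjusted total as the target, 169 per arm (338).

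In either case replace 167 with 169 per arm. The feasibility statement needs only its number updated.

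Keeping 304 costs a change of wording and a slightly less favourable power statement. Moving to 338 costs 34 more participants than the present target (338 − 304).

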#### Analysis plan

Summary statistics will be used to compare study arms descriptively with respect to baseline socio-demographic characteristics and risk factors for the outcome (e.g. new to clinic vs. poorly retained; newly diagnosed vs. not). In addition, mean duration of study follow-up will be compared by arm, and process measures (e.g. rate of response to Type 2 and 3 messages, self-reported interruptions in cell phone service) will be described.

Following the intention to treat principle, participants will be analyzed in the arms to which they were randomly allocated. Virologic suppression will be analyzed using generalized estimating equation log-binomial models [44],[45] to estimate 12 month mean (95% CI) prevalence by arm and relative risk between arms, adjusted for the stratification factor (newly diagnosed in past 12 months vs. earlier), while accounting for correlation among clustered binary responses at 6 and 12 month follow up. As described in Table 2, virologic suppression status will be missing only if the participant is both lost to the clinic and to the study during the specified data collection window. Model extensions will determine the explanatory effects on virologic suppression of 1) retention in care as a mediator of effect, and 2) intensity of SMS exposure (per protocol analysis).

A log-binomial model will also be used to estimate 12-month mean (95% CI) visit adherence rate by arm and the relative rate between arms, adjusted for the stratification factor and correlation among responses per participant. Like the virologic suppression outcome, the ordinal retention in care outcome will be evaluated for each 6-month study period. For each participant, two indicators per period will be calculated: all scheduled primary care appointments were kept (true/false) and some scheduled primary care appointments were kept (true/false). At the end of the trial, the data will be further reduced to two indicators: all scheduled primary care appointments kept in both periods or some scheduled primary care appointments kept in both periods. Trial-level outcomes will be analyzed using an ordinal logistic regression model to estimate threshold-specific mean (95% CI) odds of retention in HIV care by arm and odds ratios between arms, adjusted for the stratification factor and number of scheduled study visits. If model diagnostics indicate that the proportional odds assumption does not hold, each threshold (all kept vs. fewer than all kept; some/all kept vs. none kept) will be modeled via a logistic regression model. A model extension will analyze study period-level outcomes.

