### Study objectives

#### Primary objective

To determine whether the C4C intervention improves virologic suppression at 12 months when compared to SMS appointment reminders alone.

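### The primary model combines 6- and 12-month suppression without fixing how its single relative risk becomes the month-12 effect

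*Protocol article*

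**What the plan says.** The Primary objective section of the protocol article reads: "To determine whether the C4C intervention improves virologic suppression at 12 months when compared to SMS appointment reminders alone". The Primary outcome section agrees: "The primary outcome is virologic suppression at 12 months". The Sample size section also works at month 12, with 60% suppression in the control arm and an improvement of 15 points.

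The Analysis plan then gives the model: "Virologic suppression will be analyzed using generalized estimating equation log-binomial models". Its purpose is "to estimate 12 month mean (95% CI) prevalence by arm and relative risk between arms, adjusted for the stratification factor", and this is done "while accounting for correlation among clustered binary responses at 6 and 12 month follow up". So both follow-up visits supply responses, one relative risk is requested, and the stratification factor is the only adjustment listed. The extensions listed for suppression are mediation ("Model extensions will determine the explanatory effects on virologic suppression of 1) retention in care as a mediator of effect") and intensity of SMS exposure. A period-level extension is named in the paragraph on retention.

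Under Inclusion criteria, every participant must have a viral load above 200 within the 4 weeks before entry, so a baseline value exists for all. Under Randomization, the reason given for stratifying is that suppression in the newly diagnosed "may exceed the rate among individuals with longer standing HIV diagnoses".

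**The concern.** A model that takes two visits per person and has one arm coefficient estimates one ratio for both visits. If the effect builds over the year, that ratio understates the month-12 effect. If the effect fades, it overstates it. The design makes neither pattern implausible: everyone starts unsuppressed and messages run for a full year, so an effect could grow, while the phone-service interruptions that the article anticipates could weaken it.

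The wording does not settle the matter. A 12 month mean prevalence may be the mean at month 12, but the next paragraph of the Analysis plan uses the same expression for the visit adherence rate, which accrues over the year. Two analysts following this text could report different primary results from the same data. At stake is whether the headline RR and its test answer the stated primary objective.

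**Working it through.** **Inputs from the article.** Month-12 suppression 60% in the control arm, +15 points with the intervention (75%, so RR = 0.75/0.60 = 1.25), 80% power, two-sided 0.05, 152 per arm, 1:1 allocation.

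**Inputs assumed, because the article gives none.** Control rate at month 6: 50% (range 40–60%). Month-6 RR: 1.00 to 1.30. Within-person correlation: 0.3 to 0.7.

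**1. The plan's own figure.** Two proportions, pooled variance under the null, no continuity correction, mean proportion 0.675:

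n = [1.96·√(2·0.675·0.325) + 0.842·√(0.60·0.40 + 0.75·0.25)]² / 0.15² = 151.9, so 152 per arm. This reproduces the stated number and confirms that the trial was sized for a month-12 comparison.

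**2. The RR from a model with arm and stratum only.** With equal numbers at each visit and a log link, the arm coefficient is the ratio of the two-visit average prevalences:

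RR = (p6,int + p12,int) / (p6,con + p12,con)

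Month 12 is held at 75% vs 60%, and the month-6 control rate is 50%:

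| Month-6 RR | Month 6, intervention | Calculation | RR from the model |
|---|---|---|---|
| 1.00 | 50% | 1.25/1.10 | 1.14 |
| 1.10 | 55% | 1.30/1.10 | 1.18 |
| 1.25 | 62.5% | 1.375/1.10 | 1.25 |
| 1.30 | 65% | 1.40/1.10 | 1.27 |

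With no month-6 effect and a month-6 control rate of 40% or 60%, the result is 1.15/1.00 = 1.15 or 1.35/1.20 = 1.125.

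The reverse case, a month-6 RR of 1.25 and no month-12 effect: (0.625 + 0.60)/(0.50 + 0.60) = 1.11, although the true month-12 RR is 1.00.

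**3. Check by simulated GEE** (log link, Poisson variance, exchangeable correlation, 40,000 per arm, true month-12 RR 1.25):

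| Month 6, control vs intervention | Arm + stratum | + visit | Arm × visit, month-12 RR |
|---|---|---|---|
| 50% vs 50% | 1.13 | 1.14 | 1.24 |
| 50% vs 57.5% | 1.205 | 1.21 | 1.25 |
| 50% vs 62.5% | 1.25 | 1.25 | 1.25 |
| 60% vs 75% | 1.255 | 1.255 | 1.25 |

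A visit main effect alone does not recover the month-12 RR; the arm-by-visit term does.

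**4. Consequence for the test** (Wald test of log RR, 152 per arm). For month 12 alone, SE = √[(0.40/0.60 + 0.25/0.75)/152] = 0.0811, and power = Φ(0.2231/0.0811 − 1.96) = 79%. For the two-visit average, the variance of a person's mean is [p6(1−p6) + p12(1−p12) + 2ρ√(p6(1−p6)p12(1−p12))]/4. Over ρ from 0.7 to 0.3, with a 50% month-6 control rate:

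- no month-6 effect: power 31–39%
- month-6 RR 1.10: power 49–60%
- month-6 RR 1.25: power 76–86%
- month-6 RR 1.25 and no month-12 effect: significant in favour of the intervention in 22–28% of trials, against a nominal 2.5% in that direction.

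**5. Log link.** Under a constant RR of 1.25, a stratum with an 80% control rate has a fitted probability of 0.80 × 1.25 = 1.00, the edge of the parameter space.

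**6. Baseline viral load.** In simulations of 304 participants comparing the standardised risk difference with and without the covariate, the variance ratios were 0.98, 0.96 and 0.88 for assumed log-odds of 0.3, 0.5 and 0.8 per SD. That is a reduction of about 2–12%.

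**The case against.** The strongest reply is that the article does name a 12 month target, in line with its objective, outcome and sample size, and that the phrase on stratification describes an adjustment and is not a complete list of model terms. Accounting for correlation concerns the covariance, not the mean. The paragraph on retention also says that its ordinal outcome is evaluated per 6-month period as suppression is, which fits visit-specific estimation. A full analysis plan may contain the visit terms.

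Much of this stands. A reader might infer that the plan has chosen a two-visit average as its estimand; the document does not say so. What remains is that the article specifies family, link, adjustment and clustering but not the contrast that delivers month 12. Its key phrase has two readings, and evaluated per period may mean only measured per period.

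It is also fair that the month-6 inputs are assumed and that the discrepancy is zero when the two RRs are equal.

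Two further readings are tempting and unsupported. One is that omitting baseline viral load or entry route is an error. Under randomization the omission does not bias the RR and contradicts nothing in the article, which names entry route only for descriptive comparison. The other is that the log-binomial model should be expected to fail. The article says only that the newly diagnosed rate may be higher and gives no stratum rates. Simulated failure rates depended heavily on an assumed constant RR: with a constant odds ratio of 2 they were 0–3% at newly diagnosed control rates of 70–80%.

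**Conclusion.** The point holds as a lack of definition in the primary analysis, not as a proven mismatch. If the model is fitted with only the terms listed, its RR is a two-visit average. For a true month-12 RR of 1.25 and an assumed 50% control rate at month 6, it ranges from 1.14 (no month-6 effect) to 1.27 (month-6 RR 1.30), and it is exact only when the month-6 RR is also 1.25. In the least favourable of these cases, power falls from 79% to about 31–39%. These sizes rest on assumed month-6 rates and correlations and are illustrations, not forecasts. The wording should be settled before analysis because the primary estimate and test depend on it. Baseline adjustment is a precision gain only, and a convergence fallback is optional.

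**What to change.** State that the GEE mean model contains arm, visit, arm-by-visit and the stratification factor, and that the arm contrast at month 12 is the primary test and estimate. Replace the reference to a 12 month mean with prevalence at month 12. Any two-visit average should be labelled secondary.

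Add baseline log10 viral load, already obtained for eligibility, as a covariate for precision. Optionally, name modified Poisson GEE with robust variance as the fallback if the log-binomial model does not converge.

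The cost is wording in the analysis plan; no new data are needed. The month-12 contrast gives up some precision relative to a two-visit average when the effect is constant. For a constant RR of 1.25, power is about 79% for month 12 alone, against 76–86% for the average if the month-6 control rate is 50%, and 85–93% if it is 60%. Since 152 per arm was calculated for month 12, the design does not rely on that extra precision.
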